At the individual level, women lack knowledge of their risk factors and the role of screening as a prevention and early detection tool [4,21,22]. These factors, along with fear of the tests, limit their personal agency to seek screening [6,7,26]. At the interpersonal level, social norms that perpetuate fatalism, cancer stigma, and gender roles in decision-making also discourage care-seeking behavior [26-29]. At the structural level, barriers include provider knowledge, discomfort discussing sensitive topics [21,30], provider stigma, and inadequate communication of test results. For example, more than one-third of women did not receive their test results in a screening pilot study in Nyeri County [31].

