### Implementation Strategies

Women enrolled in the C3Link Core and Plus communities will receive a package of strategies delivered by study CHWs in the community setting. CHWs are community members who receive standardized training to collect data on demographics and health needs in their communities while supporting management of minor ailments and making referrals for other ailments. Each CHW supports up to 100 households. In Kenya, they are referred to as community health promoters.

CHWs play an important role in addressing individual and interpersonal barriers to improve knowledge and encourage women to seek medical care. In order to optimize available resources, we will adopt a tiered process through which only women who require multiple strategies are offered them. We will include a C3Link Core group receiving education sessions only where CHWs deliver group education sessions to women and their support persons, a C3Link Plus group will receive the C3Link Core group education sessions and later add on individual evidence-based strategies that increase in resource intensity in a sequential order, targeting women who remain unscreened at 1-month intervals, and a third group receiving enhanced usual care (ie, distribution of flyers in addition to usual care).

At the clinic level, C3Link Core and Plus strategies will use practice facilitation in clinics to foster team-based care with CHWs embedded within the clinic teams to build optimal community linkages and communication channels. CHWs serving as team members in the clinic setting can cocreate optimal processes in screening clinics to coordinate the return of test results to women and support completion of follow-up recommendations. We will provide education to health care providers to improve communication and reduce any stigmatizing behaviors. Through the practice facilitation process, we will implement a learning collaborative that offers peer-to-peer consultations to improve screening capacity.

The enhanced standard-of-care communities will not have any CHWs. During enrollment, we will distribute campaign flyers provided by the National Cancer Institute of Kenya. Women who visit clinics may benefit from quality improvement processes. Table 1 provides details on the activities and goals of strategies during each phase of this study.

**Table 1. T1:** Training and delivery of the multicomponent strategies.

Setting—Goal	C3Link^a^ Core and C3Link Plus	Enhanced standard of care

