### Women Requiring Follow-Up Procedures

Study CHWs will inform participants within communities when HPV test results become available. During the HPV test results collection and breast cancer screening visit, providers will inform participants who require diagnostic procedures or treatment. Otherwise, for women who will not go to the clinics for their results and/or breast cancer screening, study CHWs will contact them after 2 weeks—encouraging them to visit their respective clinics, and providing navigation to support completion of required tests or treatments as needed. As in prior pilot studies, these procedures will be financed through Kenya’s Social Health Authority with supplementation from this study when necessary.

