### Data Collection

To assess the impact of the C3Link Core and Plus strategies on the mediating outcomes, we will conduct surveys to collect data from women, support persons, and providers in the clinics. Study CHWs will document strategy implementation in the C3Link CHW tracking tool, and this information will be used to determine the “dose of the intervention” (ie, in the community setting, dose is the number of education sessions attended or the type of individual-level intervention). We will track all health care service use of women enrolled in this study by conducting clinic audits at all 9 clinics and referral facilities. Data will be collected using tablets, which will contain REDCap (Research Electronic Data Capture; Vanderbilt University) programs to collect and store the data. Deidentified data will be transferred and stored in secure, password-protected servers. Research Triangle Institute (RTI) and Implenomics staff will conduct further data quality review, produce reports, and develop analytic files for collaborative analysis. Tables2  3 present end point definitions and biological, imaging, self-report, and clinic audit data collected at baseline and to be collected at 12-, 24-, and 36-month follow-ups.

**Table 2. T2:** Data collection at baseline, 12 months, 24 months, and 36 months. Data elements for primary, secondary, and follow-up end points—cancer care continuum.

Constructs or measures	Instrument and specification	Source	Timing
Proportion of women undergoing recommended cancer screening (primary end point measured at 24 months)	Cervical: Papanicolaou test (cytology laboratory), HPV^a^ DNA (Roche Cobas platform or Cepheid GeneXpert); breast: CBE^b^ or mammograms	Biological, imaging, and clinical procedures identified through clinic audits and this study’s database	12, 24, and 36 months
Proportion completing supplemental and diagnostic procedures in ≤90 days	Measured as days from referral to undergo procedures such as ultrasound, biopsy, colposcopy, and ablation of cervical lesions	Biological, imaging, and clinical procedures identified through clinic audits and this study’s database	24 and 36 months
Proportion of patients with cancer diagnosis initiating treatment in ≤90 days	Measured as days from cancer diagnosis to start of treatment; prespecified abstraction tool to identify dates and procedures	Biological, imaging, and clinical procedures identified through clinic audits and this study’s database	24 and 36 months

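### Timing follow-up completion from referral can leave out HPV-positive women whose results never reach them, so the Hypothesis 2 comparison may understate the benefit of Core and Plus

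*Protocol article*

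**What the plan says.** The protocol article's Data Collection section presents Table 2 as giving end point definitions. The follow-up row reads "Proportion completing supplemental and diagnostic procedures in ≤90 days" and specifies it as "Measured as days from referral to undergo procedures such as ultrasound, biopsy, colposcopy, and ablation of cervical lesions". It gives no denominator, no definition of the referral date and no rule for a woman with a positive result but no referral.

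The section Women Requiring Follow-Up Procedures describes how a woman learns of her result:

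- Announcement: "Study CHWs will inform participants within communities when HPV test results become available".
- Results visit: "During the HPV test results collection and breast cancer screening visit, providers will inform participants who require diagnostic procedures or treatment".
- Women who do not come: "study CHWs will contact them after 2 weeks—encouraging them to visit their respective clinics", with navigation as needed.

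Under Implementation Strategies, CHWs working in the Core and Plus clinic teams help to "coordinate the return of test results to women and support completion of follow-up recommendations". For control the same section says: "The enhanced standard-of-care communities will not have any CHWs".

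The Background section treats uncollected results as a known barrier: "more than one-third of women did not receive their test results in a screening pilot study in Nyeri County".

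Hypothesis 2 expects better compliance with follow-up referrals in Core or Plus than in control. Table 2 marks only screening uptake as primary, but the Results section places completion of follow-up diagnostic tests in the 24-month primary end point analysis.

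**The concern.** Time from referral can be computed only for a woman who has a referral. If the referral normally follows collection of the result, the set of women being timed is formed after randomisation, by a step on which the intervention acts. CHWs announce results and pursue non-attenders in Core and Plus; nobody in the study does so in control.

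Three HPV-positive women show the effect, if completers are counted among the referred:

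- A control woman whose result never reaches her has no referral. She counts neither as a success nor as a failure.
- A similar woman in Core is reached by a CHW, referred, and does not go. She counts as a failure.
- A woman in any arm whose result waits a long time before she is referred, and who then has the procedure within 90 days of referral, counts as a full success. The wait is not recorded in the end point.

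At stake is the Hypothesis 2 comparison. It could show little or no difference while more HPV-positive women in Core and Plus complete follow-up. The absolute completion figure would also be too high, as a statement about women with positive results, wherever results go uncollected. The article further plans to use each arm's service use along the care continuum as input to its simulation models. A rate among referred women would overstate completion there if it were applied to all positives.

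**Working it through.** The article gives no expected rate, sample size or power for the follow-up end point, so there is no figure of its own to reproduce. What follows is an illustration for HPV-positive women.

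**Inputs**

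- Result return in control, r_C = 0.667. This is anchored on the Background figure of more than one-third not receiving results, so 0.667 is an upper value for that pilot. Applying it to HPV-positive control women is an assumption.
- Result return in Core/Plus, r_T = 0.90, range 0.80 to 1.00. Assumption.
- Completion within 90 days after referral among women who would attend anyway, c = 0.70, range 0.60 to 0.80. Assumption.
- Completion among the extra women recovered by CHWs, c2. Assumption, varied below.
- A woman is referred if and only if her result reaches her. This is the natural reading, not stated text.

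**Formulas**

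- Among the referred: control = c; Core/Plus = [r_C × c + (r_T − r_C) × c2] / r_T.
- Among all positives: control = r_C × c; Core/Plus = r_C × c + (r_T − r_C) × c2.

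**Case 1: equal completion after referral (c2 = c = 0.70)**

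- Referred: 70% v 70%, difference 0.
- All positives: 0.667 × 0.70 = 46.7% v 0.90 × 0.70 = 63.0%, difference 16.3 points.
- Smallest difference over the ranges: (0.80 − 0.667) × 0.60 = 8.0 points.
- Largest: (1.00 − 0.667) × 0.80 = 26.6 points.

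**Case 2: recovered women complete less often (c2 = 0.50), no navigation effect on the others**

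- Referred: (0.667 × 0.70 + 0.233 × 0.50) / 0.90 = 0.583 / 0.90 = 64.8% v 70% in control, difference −5.2 points.
- All positives: 58.3% v 46.7%, difference +11.6 points.

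**Case 3: as case 2, but navigation raises completion to 0.80 in women who would attend anyway in Core/Plus**

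- Referred: (0.667 × 0.80 + 0.233 × 0.50) / 0.90 = 0.650 / 0.90 = 72.2% v 70%, difference +2.2 points.
- All positives: 65.0% v 46.7%, difference +18.3 points.

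**Case 4: navigation raises completion to 0.80 in all referred Core/Plus women**

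- Referred: 80% v 70%, difference +10 points.
- All positives: 0.90 × 0.80 = 72.0% v 46.7%, difference +25.3 points.

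In all four cases the comparison among the referred falls short of the comparison among all positives. It changes sign only in case 2.

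**Dilution.** The end point also covers breast follow-up. If HPV-positive women make up a share w of all women needing follow-up, and no breast finding is lost before referral, the difference missed in case 1 is w × 16.3 points. With w = 0.5, an assumption, that is 8.2 points.

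**The case against.** The strongest reply is that the article does not say what the concern needs it to say.

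- **Referral only at attendance.** A reader might infer that a referral exists only once a woman comes for her result. The text says that providers inform women at that visit; it does not define when a referral is made. Table 1 has results and referrals conveyed with CHW support, and the Objectives section has CHWs returning results to women. This stands: the referral step is inferred. But any referral carried by a CHW to a non-attender could occur only in Core and Plus, so the referral date would then mean different things by arm.
- **Denominator.** It is not stated, and a full protocol or SAP may state it. This also stands. What the article does fix is the clock, and days from referral have no value for a woman without one.
- **Fit with the hypothesis.** Hypothesis 2 is worded as compliance with referrals, which time from referral does measure. That is a reason to keep it as a supporting measure. It does not remove the arm-dependent selection of the women being compared.
- **Result return is measured elsewhere.** Table 3 includes the percentage of results shared within 2 weeks and the number of follow-up tests done. So the benefit is not lost to the trial. Neither item, however, links a positive result to a completed procedure.
- **Size.** The one-third figure concerns all women in a Nyeri pilot, not HPV-positive women. The Objectives section cites the same pilot as evidence that CHWs help uptake, so it is not clearly a rate without CHWs. Control women use the same nine clinics and may gain from their training. All of this stands, and it makes the numbers illustrative.
- **Reversal.** A reader might infer that the comparison will come out in the wrong direction. The documents do not support that. It requires CHW-recovered women to complete less often and navigation not to make up the difference.

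**Conclusion.** The point holds in a limited form. The article fixes a clock that starts at referral, a step after randomisation that CHWs are there to influence and that has no study CHW support in control. Read naturally, the end point leaves out women whose positive result never reaches them and ignores delay before referral. The comparison can therefore understate the benefit of Core and Plus.

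With equal completion after referral, the missed benefit among HPV-positive women is 8 to 27 points under the assumed ranges, and it shrinks in the combined end point in proportion to the cervical share. This rests on a control return rate borrowed from a pilot of all women and on assumed rates for everything else. If navigation also improves completion after referral, a benefit can still show, though a smaller one than among all positives.

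The documents do not support saying that referral occurs only at attendance, that unreached women are excluded by a written rule, or that the result will be reversed. The problem is mainly one of cervical screening; no comparable delay is shown for clinical breast examination.

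**What to change.** In Table 2:

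- For cervical screening, start the 90-day clock on the date the abnormal result became available.
- Use as denominator all screened women whose result calls for supplemental or diagnostic follow-up under the study's standard operating procedures. Count those never reached or never referred as not completed.
- Apply the same denominator to breast findings, where the examination and referral dates will usually coincide.
- Define the referral date so that it means the same thing in all arms.
- Keep days from referral as a supporting measure, splitting the delay into result to referral and referral to procedure.

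The cost is one extra date in the abstraction tool; test results already come through the clinic audits and study database. The follow-up analysis is not due until 2027. Completion percentages will be lower in every arm, and the article should say why. The denominator remains conditional on having been screened, which also differs by arm; completion as a proportion of all enrolled women would be a useful sensitivity analysis.

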### Data Analysis

Hypothesis testing will be carried out by intent to treat, and we will examine the effects at the individual level across the 3 randomization groups. We will use generalized estimating equation models to estimate the effects of the randomization groups. If the Hausman assumption of correlation between the random and fixed effects is violated, then we will include fixed effects representing cluster identification [71]. We will adjust for baseline covariates, including sociodemographic and behavioral factors, should the initial descriptive analyses suggest differences in the distribution of these factors across study randomization groups. We will also explore the use of propensity scores to control for systematic differences between the groups. In further analyses, we will compare differences in mediating outcomes across the groups and examine the potential moderating roles of key individual behavioral, social, and structural factors hypothesized to influence cancer screening and adherence along the cancer care continuum, as shown in Figure 1. We will test the “dose” of the C3Link Core and Plus strategies received as a covariate in these models. We will explore differences in breast and cervical cancer screening completion and report the proportion that complete at least one of the screenings. As appropriate, we will perform analyses separately or pooled together for the younger and older cohorts of women to assess whether care-seeking behavior differs by age group. A key aspect of interest in this study is the extent to which perceived and anticipated stigma affects care-seeking behavior and screening completion. In subsequent analyses, we will consider both medium-term outcomes within the first 12 months after enrollment and changes at any point during the 24-month and 36-month follow-up period to assess longer-term outcomes. To understand potential variation across communities, we will conduct comparisons to analyze differences in mediating and screening outcomes among each of the C3Link Core and Plus communities. We will also report on the overall quality of the screenings provided, women’s preferences for cervical cancer screening, and the type of procedures used along the continuum of care. For the C3Link Plus arm, we will document the increase in screening completion with each step in the series of individual strategies and the number of women requiring each type of strategy.

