**Methods:**

We will create the C3Link package aimed at increasing breast and cervical cancer screenings, and adopt a study design to assess and evaluate sustainability in 3 counties: Machakos, Nakuru, and Nyeri. Three noncontiguous communities for each of the 9 study clinics (3 per county) will be randomly assigned to one of the study arms using the R (R Foundation) program. The intensity of the strategies varies from low (awareness campaign for the enhanced usual care arm), to medium (C3Link Core arm with study community health worker–led group education and study community health worker–embedded clinic teams enhanced with practice facilitation), and to high (C3Link Plus arm with C3Link Core and a predetermined sequence of individual strategies). Women aged 30 to 55 years (1 per household) will be eligible to participate and could select a support person for inclusion. Trained data collectors will conduct surveys for women, their support persons, and from providers in the clinics using questionnaires, tracking tools, and focus group discussion guides. We will collect data and conduct interviews and focus groups to identify underlying moderating factors associated with the successful implementation of strategies. We will use implementation science methods to evaluate the effectiveness, implementation outcomes, and cost-effectiveness of the C3Link program compared with the enhanced usual care.

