### Study Design and Sample Size Determination

The sample size was determined using standard parameters (*α*=.05, 2-sided tests), based on the primary end point and allowing for the detection of a 15 percentage point improvement in the primary end point, our minimum threshold to consider the C3Link package of strategies to be successful. For the enhanced standard-of-care arm, given the current low level of screening, we estimated the screening uptake for both cancers to be about 15% at the 24-month follow-up (end of intervention phase). With a sample size of 100 in each of the 9 communities in the trial arms (for a total of 2700 women, and each woman will select 1 family member or support person), we will be able to detect a 15% difference with over 80% power, even after accounting for up to 20% attrition at 24 months. We selected a screening uptake of at least 30% in either the C3Link Core or Plus arm on the basis of prior study results [62,63]. We estimate that the interclass correlation coefficient would be in the range of 0.03 to 0.05 because interclass correlation coefficients for binary data are typically quite small, especially when screening uptake is very low [64]. Furthermore, we anticipate that the C3Link Plus arm would achieve a higher uptake than the C3Link Core arm, and we would be able to detect any difference of 15 percentage points between this study’s arms (ie, screening uptake of 15%, 30%, and 45% in the enhanced standard-of-care, C3Link Core, and C3Link Plus arms, respectively) with over 90% power. In each community, we will select study participants, 1 woman per household, using the Kish method [65], with eligibility remaining the same as previously stated. We will oversample by 10% to account for participants who cannot be contacted, refuse to participate, or are no longer eligible. The C3Link study cluster randomization is presented in Figure 2.

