### Recruitment

The 3 communities per study clinic will be randomly assigned to one of the following study arms: C3Link Core, C3Link Plus, or enhanced standard of care. Trained study data collectors and study CHWs will visit households in the selected communities with the help of county CHWs (promoters). They will visit households in selected communities and enroll eligible women. Women will be eligible to participate if they are 30 to 55 years of age to capture most cases of persistent HPV infections (lower age limit) and those within the peak age groups of breast cancer incidence rate in Kenya (higher age limit). These women will be due to receive both breast and cervical cancer screening during this study’s intervention phase based on Kenyan guideline recommendations, not experiencing breast or cervical cancer symptoms, not pregnant, fluent in a study language (English, Kiswahili, Kamba, Kalenjin, and Kikuyu), and have plans to remain in the community for at least 2 years. We will include women who meet the inclusion criteria (1 per household using the Kish method) [65].

The study CHWs will administer a short survey to all women to assess eligibility for this study. The data collectors will administer the baseline survey to women who will give voluntary informed consent to participate. Each enrolled woman will be allowed to select a support person (spouse or community member) older than 18 years of age—the legal age for consent for health research in Kenya, with help from their CHW if needed. Selecting a support person will be voluntary. Study CHWs will administer a support person eligibility checklist tool before data collectors administer the support person baseline survey to those who give voluntary informed consent.

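### The Hausman fallback, read as fixed effects for the randomised communities, would absorb the arm effect; the main GEE is unaffected unless the fallback is triggered

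*Protocol article*

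**What the plan says.** All references are to the protocol article.

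- **Randomised unit.** The Abstract (Methods) states: "Three noncontiguous communities for each of the 9 study clinics (3 per county) will be randomly assigned to one of the study arms". Recruitment repeats it: "The 3 communities per study clinic will be randomly assigned to one of the following study arms". Study Design and Sample Size Determination gives nine communities per arm, hence 27 communities in nine clinics. Every woman in a community has that community's arm.
- **Primary end point.** Table 2 in Data Collection makes the proportion screened at 24 months primary, so the main comparison is between arms at one time point.
- **Main model.** Data Analysis states: "We will use generalized estimating equation models to estimate the effects of the randomization groups".
- **Fallback.** The next sentence reads: "If the Hausman assumption of correlation between the random and fixed effects is violated, then we will include fixed effects representing cluster identification". It does not say whether the cluster is the community or the clinic. It gives no other route to the arm effect once these terms are in the model.

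**The concern.** Arm does not vary within a community. If the fallback means indicators for the randomised communities, they explain everything that arm could explain, and no between-arm contrast is left to estimate. Software would then either drop the arm terms or drop two community indicators. In the second case the coefficient labelled as arm becomes a contrast between single communities, and its value depends on which ones were dropped. The team would have to improvise a replacement with outcome data in hand.

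The trigger adds to the problem. A Hausman test compares a random-effects with a fixed-effects estimator, and a GEE has no random effects. Arm was randomised, so it is independent of the community effects by design. Because arm is constant within communities, the fixed-effects estimator gives no arm coefficient to compare. The test could therefore respond only to woman-level covariates. A chance imbalance in one of them could invoke a rule that removes the effect of interest.

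**Working it through.** **Inputs.** 27 communities, three in each of nine clinics, nine per arm (Abstract; Recruitment; Study Design and Sample Size Determination). One community per arm in each clinic is the natural reading of the Recruitment sentence. It agrees with Qualitative Feedback, which has nine Core and nine Plus community health workers, six per county. From the sample size section: 100 women per community, up to 20% attrition (so m = 80), ICC 0.03 to 0.05, uptake 15% against 30%, two-sided alpha 0.05.

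**1. The plan's own figure.** This confirms that the community is the cluster behind the power statement of over 80%.

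- Design effect = 1 + (m − 1) × ICC: 1 + 79 × 0.03 = 3.37, and 1 + 79 × 0.05 = 4.95.
- Effective n per arm = 9 × 80 / design effect: 720 / 3.37 = 213.6, and 720 / 4.95 = 145.5.
- Two-proportion power at 15% against 30%: 96.3% and 86.9%. With a t reference on 16 df: 94.3% and 83.2%.

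The stated power reproduces, so this point does not rest on the sample size.

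**2. Main GEE.** Intercept plus two arm indicators: 3 columns, rank 3. Both arm contrasts are estimable.

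**3. Fallback read as community.**

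- Intercept plus 26 community indicators: 27 columns, rank 27.
- Adding two arm indicators: 29 columns, rank still 27.

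Each arm indicator is the exact sum of its nine community indicators, and the within-community variance of arm is 0. Both arm contrasts are lost. Woman-level covariates cannot restore them, because arm still does not vary within a community. The result holds for any link function, since it concerns the linear predictor.

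**4. Fallback read as clinic.**

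- Intercept plus eight clinic indicators: 9 columns, rank 9.
- Adding two arm indicators: 11 columns, rank 11.

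Both arm contrasts are estimable, because all three arms occur in every clinic.

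**5. What clinic effects might gain.** On a standardised scale the variance of a community mean is ICC + (1 − ICC)/m. At ICC 0.05 and m = 80 this is 0.05 + 0.95/80 = 0.0619. If a share s of the between-community variance lies between clinics, clinic effects reduce it to (1 − s) × 0.05 + 0.95/80. The article gives no value for s, so a range is shown:

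| s (assumed) | Variance | SE ratio | SE reduction |
|---|---|---|---|
| 0 | 0.0619 | 1.000 | none |
| 0.25 | 0.0494 | 0.893 | 11% |
| 0.50 | 0.0369 | 0.772 | 23% |
| 0.75 | 0.0244 | 0.628 | 37% |

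Residual cluster-level degrees of freedom with clinic effects: 27 − 9 − 2 = 16.

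**The case against.** **The rule is conditional.** This stands. A reader might infer that the primary treatment effect cannot be estimated at all. The document does not support that: the GEE is stated first and its arm effects are estimable. Only the fallback branch fails, and nothing in the article says how likely it is to be reached.

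**Cluster may mean clinic.** The sentence names no level, and both the reference it cites and the randomisation figure are unavailable here. If clinic was meant, arm is estimable. Community is the more natural reading, because it is the unit that was randomised. Even on the clinic reading the sentence needs to say so, and the Hausman trigger would still have no proper basis.

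**Repeated measures.** The Data Analysis section covers all hypotheses. Self-efficacy, social support and knowledge are measured at baseline and at later visits. With two time points, arm-by-time terms survive community effects (rank rises from 28 to 30). This does not rescue the 24-month between-arm comparison. It is a reason to limit the deletion to that comparison.

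**Inferences that go too far.** A reader might also conclude that the plan uses an uncorrected sandwich test, or that it wrongly leaves clinic out. Neither is supported. The article names no variance estimator, reference distribution or full covariate list, and a condensed article may leave these to the analysis plan. In simulation, an uncorrected sandwich z test comparing nine with nine communities of 80 rejects roughly 8 to 9% of the time at a nominal 5%. The article does not specify that test, and the simulation was unblocked, so it neither shows an error here nor validates the clinic model.

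**The Hausman wording.** Naming correlation as the assumption reverses the usual null, but it can be read as loose drafting and changes no result.

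**Conclusion.** The concern holds for the fallback branch. With fixed effects for the 27 randomised communities, the 24-month between-arm effect is not identified (29 columns, rank 27). This is structural: it needs only that each community is wholly in one arm, and it does not depend on the ICC, uptake or attrition. It does depend on reading the cluster in that sentence as the community. The trigger is unsuitable at either level.

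The main GEE is unaffected unless the fallback is triggered. Choice of variance estimator and absence of clinic terms are not errors in this document. The 23% reduction in standard error is an illustration under an assumed half share of variance, not an established loss.

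**What to change.** - Delete the Hausman fallback for the between-arm comparison.
- State the model as a GEE clustered on the 27 communities, with arm as the effect of interest.
- If fixed effects are wanted, specify them in advance for the nine clinics, as the randomisation blocks, and not on the outcome of a test.
- It is sensible to state alongside this a small-sample variance correction with a t reference on about 16 df (27 − 9 − 2 with clinic effects).
- If community effects are wanted for outcomes measured repeatedly, say so separately and name the arm-by-time contrast as the target.

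**Cost.** Analysis wording only, with no new data or participants. Clinic terms use eight degrees of freedom and bring no precision gain if clinics do not differ. The Results section places the primary analysis in early 2027, so the wording should be settled before the 24-month outcomes are examined.
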